### Eligibility criteria {10}

#### Inclusion criteria

Migraine patients: patients with frequent EM (≥ 8–14 headache days/month, of which 4 fulfill IHS criteria for migraine) or CM (≥15 headache days/month, of which 8 fulfill criteria for migraine) OR Post-MO(H)-patients: patient who underwent treatment for MO(H) (initially ≥ 15 headache days/month, intake of attack aborting medication on 10 or more or 15 or more days/month according to ICHD-3 criteria of MOH) AND 2)Owning a mobile device with an iOS or Android system, which is able to run the app3)Adults ≥ 18 years4)Written informed consent consistent with ICH-GCP guidelines and local laws signed prior to all study-related procedures5)Compliance for using the app on ≥ 80% days during the screening period

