#### Exclusion criteria

Patients with concomitant primary headache disorders, other than EM or CM (except episodic tension-type headache < 15 days/month)Current MO upon the discretion of the treating physician (intake of attack aborting medication on ≥10 days/month within the last 3 months)Co-morbidity interfering with the study outcomes upon the discretion of the treating physicianIntake of opioids on > 3 days/monthRegular intake (> 15 days/month) of either (i) hypnotics or (ii) benzodiazepines as sedatives (tranquillizer) or (iii) antipsychotics (neuroleptics) due to a psychiatric indicationParallel use of other migraine apps to track headache days and medication intake

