### Outcomes {12}

#### Primary outcome

The primary outcome was defined due to its relevance to estimating MO prevalence and the associated costs [8].Proportion of patients developing MO or MOH for at least 3 consecutive months between baseline and end of study visits.

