### *Sample size {14}*

The sample size calculation is based on the comparison of two independent proportions using a *z*-test at a significance level *α* = 0.05. Calculations were performed using PASS 13. Based on data from the literature [10–12], we estimate the transition rate from frequent EM/CM to MOH to be 10% per year, and the relapse rate after MO(H) treatment to be 40%. Plausible target occurrence rates for the treatment groups are 4% in the migraine category and 25% in the post-MO(H) category [10–12], which correspond to effect sizes (relative reduction rates) of 60% in the migraine category and 38% in the post-MO(H) category.

Aiming at a power of 1−*β*= 0.8, a sample size of N_mig_ = 2 × 283 = 566 patients for the migraine category is necessary for the ITT analysis to detect a difference in MOH occurrence proportion of 6 percentage points between patients receiving direct feedback and patients receiving unspecific messages. With the same values for significance and power as above, a sample size of N_MO(__H)_ = 2 × 152 = 304 patients for the post-MO(H) category is necessary to detect a proportion difference of 15 percentage points in MO(H) relapse.

We increased the sample size to N_mig_ = 624 and N_MO(H)_ = 336 in the studied categories to compensate for loss to follow-up; thus, a total *n* = 624 + 336 = 960 patients are to be recruited for the trial.

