#### Outcome assessment

Relevant clinical data and additional lifestyle factors include information about depression, anxiety disorder, chronic back pain, sport activities, smoking, and drinking behavior as well as shift work.

The primary outcome is MO or MOH defined according to International Classification of Headache Disorders (ICHD-3, 8.2) criteria of MO and MOH [13]. According to ICHD-3, MO is defined as regular overuse of acute or symptomatic headache medication (on ≥ 10 days/month with specific migraine medication or ≥15 days/month of simple analgesics) for more than 3 months and MOH is defined as headache occurring on 15 or more days/month in a patient with a pre-existing primary headache and developing as a consequence of MO. In this study, the primary endpoint is reached when the intake thresholds or headache days are exceeded for ≥ 3 months [8].

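### The primary-endpoint rule lets headache days alone count as an event, which contradicts the plan's own definition of MOH and would count persistent chronic migraine without overuse

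*Protocol article*

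**What the plan says.** The protocol article describes the primary outcome in two places.

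- **Outcomes {12}, Primary outcome:** "Proportion of patients developing MO or MOH for at least 3 consecutive months between baseline and end of study visits".
- **Outcome assessment (under {18a}):** "The primary outcome is MO or MOH defined according to International Classification of Headache Disorders (ICHD-3, 8.2) criteria of MO and MOH". The section gives MO as intake on at least 10 days per month (specific migraine drugs) or at least 15 (simple analgesics) for more than 3 months. It gives MOH as headache on 15 or more days per month "in a patient with a pre-existing primary headache and developing as a consequence of MO". The next sentence sets the study's own rule: "the primary endpoint is reached when the intake thresholds or headache days are exceeded", with a duration of at least 3 months.

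Two eligibility criteria bear on this. Inclusion criteria admit "CM (≥15 headache days/month, of which 8 fulfill criteria for migraine" as a qualifying diagnosis. Exclusion criteria remove "Current MO upon the discretion of the treating physician (intake of attack aborting medication on ≥10 days/month within the last 3 months".

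The sample size section plans on transition to MOH: "we estimate the transition rate from frequent EM/CM to MOH to be 10% per year", against 4% with feedback.

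**The concern.** In the definition, overuse is a necessary part of MOH. In the study rule, intake and headache days are joined by "or", so either is sufficient. The two sentences stand next to each other and cannot both hold.

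The conflict matters because of who is enrolled. The CM entry threshold is the same number, 15 headache days per month, that appears in the MOH definition, and current overusers are kept out. The migraine category will therefore contain patients who are already at the headache-day threshold without overusing. If they stay there for 3 months after baseline, the literal rule makes them events. That is unchanged chronic migraine. It is not the transition or relapse named in Objectives {7}, in the primary outcome and in the sample size section.

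The intervention alerts on medication intake, so such events would blur the comparison. They would also have consequences for patients: under Trial design {8}, reaching the outcome means that patient and investigator are informed and usual treatment for MO or MOH follows.

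**Working it through.** **1. What the words "or headache days" add.** Under the article's definition, MOH = MO and at least 15 headache days. Then (MO or MOH) = MO, and every MOH case already meets the intake criterion. The words can add events to the rule only if headache days count without overuse. The literal reading is therefore the only one in which they change who is an event.

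**2. Whether another section repairs it.** The abstract and Primary outcome say only MO or MOH for at least 3 consecutive months. Table 1 lists a confirmation of app-based outcome events at Visits 1 to 3, but gives no criterion that requires overuse. The blinding section says that the primary endpoint is derived from app entries, and headache days are calculated by the app. None of these resolves the "or".

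**3. The plan's own sample size.** Inputs from Sample size {14}: 10% vs 4% and power 0.80. The two-sided α = 0.05 is from Statistical methods {20a} and 1:1 allocation from Sequence generation {16a}. Pooled z-test, with mean rate 0.07:

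n = [1.960·√(2·0.07·0.93) + 0.842·√(0.10·0.90 + 0.04·0.96)]² / 0.06² = 282.7, so 283 per arm.

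This matches the stated 2 × 283 = 566. The arithmetic is sound for a 10% vs 4% transition rate.

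**4. Effect of automatic events (illustration).** Let q be the share of the migraine category who count as events only because chronic migraine persists. The article gives neither the CM share nor its persistence, so q is an assumption. Two more assumptions are that q is equal in both arms and that 10% vs 4% holds in the rest. Then

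p(control) = q + (1 − q)·0.10, p(feedback) = q + (1 − q)·0.04, difference = 0.06·(1 − q).

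Power is exact binomial for the two-sided Pearson test at 0.05 with 624/2 = 312 per arm. The last column uses the formula of step 3.

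| q | example (CM share × persistence) | control | feedback | difference (points) | power, 312/arm | n/arm for 80% power |
|---|---|---|---|---|---|---|
| 0 | none | 10.0% | 4.0% | 6.0 | 0.85 | 283 |
| 5% | 10% × 50% | 14.5% | 8.8% | 5.7 | 0.61 | 497 |
| 10% | 20% × 50% | 19.0% | 13.6% | 5.4 | 0.45 | 734 |
| 24% | 30% × 80% | 31.6% | 27.0% | 4.6 | 0.24 | 1,564 |

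The absolute difference shrinks only slowly. Most of the power is lost because the added events raise the variance.

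**5. Other wording that does not agree.** Primary outcome says consecutive months, and the study rule omits this. The definition uses "at or above" thresholds, while the rule speaks of exceeding them. The definition says more than 3 months, while the rule says at least 3.

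**The case against.** The strongest reply is that the sentence is shorthand. The section opens by adopting ICHD-3, the sentence directly before the rule ties MOH to overuse, and the article speaks throughout of developing MO or MOH, which unchanged chronic migraine is not. On that view the rule only names the marker for each diagnosis and adds a duration. The article also condenses a full protocol that is not shown, so how the app endpoint was programmed is unknown. This stands as an account of what the authors may have meant, and it rules out saying that the trial will count these patients. It does not remove the contradiction, because the rule is the one sentence that says when the endpoint is reached.

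The size is also open to challenge. The planned 10% covers episodic and chronic migraine together, so it need not hold once persistent CM patients are set aside. Equal automatic events in both arms is an assumption too: the Discussion says that alerts can lead to a change of prophylaxis, which could affect headache days. Both limits stand.

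Three stronger readings are tempting, and the article does not support them.

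- A reader might infer that CM patients are events from the day of entry. Even the literal rule needs at least 3 months, so only those who persist would count, and fewer if "exceeded" means strictly more than 15.
- A reader might carry the power loss over to the post-MO(H) category. Inclusion criteria place the 15 headache days before treatment, and nothing says that these patients enter at that level.
- A reader might take the missing "consecutive" as withdrawn. The abstract and Primary outcome still state it, so this is only a wording point to align.

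**Conclusion.** The point holds as an internal contradiction in the definition of the primary endpoint. As written, the rule makes headache days sufficient without overuse, and the eligibility criteria admit patients for whom this matters. If it were programmed literally, the primary result would partly measure persistence of chronic migraine. It should be corrected before the endpoint is derived.

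The contradiction itself rests on no assumption. The power figures do: they depend on the assumed share q, on equal automatic events in both arms, and on 10% vs 4% in the remaining patients. They show that even a 5% share would be costly (0.85 to 0.61). They do not predict what this trial will see.

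**What to change.** Restate the rule in Outcome assessment so that headache days count only together with the intake threshold over the same 3 consecutive months. MO is then the intake threshold for the drug class, met in each of those months. MOH is the same criterion plus 15 or more headache days in those months.

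Align Primary outcome and Outcome assessment on three details: consecutive months, "at or above" versus "exceeded", and at least 3 versus more than 3 months. Program the app-derived endpoint, and the confirmation at visits, to that one rule.

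State openly what follows. Every MOH event is then also an MO event, so the primary endpoint is in effect MO, and MOH is a subset that can be reported separately. If the authors do want headache days to count without overuse, they should say so, and the MOH definition and the planning rates would then need to be revisited.

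The cost is one sentence in the protocol, the matching edit to the outcome wording, and the endpoint program. No new data are needed, because intake and headache days are already recorded daily.

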### Trial design {8}

This trial will be conducted according to the professional code for physicians in Germany §15 and is designed as a randomized, controlled, parallel, allocation-blinded multicenter, prospective trial with two arms. The effects of providing feedback to migraine patients regarding their self-reported use of migraine medications will be monitored using the app “N1-Headache” on the development of MO or MOH over 12 months after randomization.

Patients with qualifying migraine or a history of MO(H) will be recruited in different ways: First, through their physician at a participating headache center or medical practice. Second, through an advertisement for this trial sent by Curelator to German-speaking users of the public available Curelator app, directing interested patients to a participating site. Third, through cooperation with the German Headache Society (DMKG) and the MigräneLiga e.V, a self-help organization who will provide information about the trial within the respective section on their homepage. In addition, some study sites might publish a pre-approved template on their homepage to inform about the trial.

Informed consent will be obtained in the participating center through the investigator and a screening for the inclusion and exclusion criteria will be carried out. Medical history will be assessed for the determination of headache type and current treatment as well as actual medication intake. To facilitate the documentation of medication, the attack aborting medication documented during the screening visit will be handed out to patients as a printout to be entered in the app.

After patients have completed a screening phase of 28 days with a sufficient level of compliance (≥80% days of recording headache and medication use) and if the inclusion and exclusion criteria are still fulfilled, they will be allocated to one condition (migraine patients or post-MO(H) patients) and subsequently randomized into one of the two study groups (control group or intervention group). The control group will receive unspecific messages providing information on general trigger factors or latest migraine research highlights. The intervention group will receive the same unspecific messages and also direct feedback on their medication use through warning messages when predefined limits of frequent medication use are reached or passed.

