### Intervention description {11a}

N1-Headache is a digital platform (consisting of the N1-Headache app and the N1-Headache dashboard) that allows individuals with a history of migraine to track their headache outcomes (e.g., frequency, severity, and duration of attacks), migraine-related disability, medication use, and their potential migraine risk factors. For the MOH-DE study, the commercially available N1 platform was modified (e.g., onboarding and daily questionnaire, app settings, feedback customization) to comply with necessary study-specific adjustments and requirements.

Daily tracking of headache days, medication, and headaches and migraine risk factors is done through a visual interface that uses Visual Migraine Language^TM^ (VML), a set of icons developed with headache specialists and designed to facilitate the data entry of migraine symptoms and up to 70 migraine attack-related risk factors selected from a presented list, plus any custom factors the individual wants to track. Significant associations are presented to the user as a set of maps designed to show the results of their personal risk factor analysis.

The app is self-explanatory with a help icon behind each question where a detailed description of the question or answers is provided. In addition, a manual with all important questions is linked within the app.

Unspecific messages providing information on general trigger factors for migraine attacks or the latest migraine research highlights will be sent once a month to both groups to increase the general engagement with the app.

The intervention will be applied by means of alerts about the risk of overuse of certain classes of medication commonly used to treat headache/migraine or other conditions but which may also cause medication overuse headache. N1-Headache calculates the current risk of MO based on all the medications taken by an individual to treat migraine attacks and sends alerts to the user. Thresholds have been defined in accordance with the current ICHD-3 guidelines and are the same for all patients in the intervention arm.

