A challenge of the study is to combine the need of reliable statistical analysis tools to test the proposed study hypothesis with the need to allow fast market implementation in case of positive study results. For the post-study statistical analysis, it is of high importance that the underlying mechanisms of how study data was generated and collected is stable and robust and protected from permanent changes. These requirements are per se contradictory to the usual development cycles of mobile applications, which aim to improve the product for consumers in repeating loops. The proposed study design serves the interests of both sides due to study length and update regulations. First, a 1-year observation per patient and a total study duration of 2 years make it likely that applications on mobile devices are still a state-of-the-art technology used by a high percentage of people. Second, a steady-state application (protected from “cosmetic” updates) ensures that patients included at a later time point in the study will experience the same environment as patients enrolled early in the trial. Therefore, collected data remains comparable.

A possible limitation might be that recruiting physicians will treat both randomized patient groups more intensely than in usual care. This could lead to equipoise for the two treatment arms.

An advantage of the presented study is that the proposed study objective is suitable to be transferred to potential future technologies and therefore is quite sustainable as the platform will be a tool to answer the study question, not the cause of the obtained results. As the study wants to test the impact on direct feedback, positive results can most likely be translated to other forms of feedback as well. In the future, this does not necessarily need to be limited to app-based systems.

The strength of the study is the high number of planned patients and the rigorous design which compares the app including the electronic diary with additional warning messages if predefined thresholds of acute medication use are reached. Reaching those thresholds will result in an advice to contact the physician who will start an intervention (for example change of prophylaxis) according to clinical guidelines. Therefore, the study is part of a real-word setting and not in a totally artificial setting.

### 
Trial status

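### The sentence that scores the primary endpoint requires day-count thresholds to be exceeded, while the definition it applies counts days at or above them

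*Protocol article*

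**What the plan says.** All the conflicting text is in the Outcome assessment part of the protocol article's section on outcome collection {18a}.

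- The anchor: "The primary outcome is MO or MOH defined according to International Classification of Headache Disorders (ICHD-3, 8.2) criteria".
- The intake limits for medication overuse (MO) are inclusive: "on ≥ 10 days/month with specific migraine medication or ≥15 days/month of simple analgesics".
- The headache-day limit is inclusive too: "MOH is defined as headache occurring on 15 or more days/month".
- The scoring rule, stated for this study and for a duration of three months or more, is not: "the primary endpoint is reached when the intake thresholds or headache days are exceeded".

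The Primary outcome section {12} asks for at least three consecutive months and gives no day count. The eligibility criteria {10} use inclusive limits both for the history of treated MO(H) and for the exclusion of current overuse.

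On the intervention side, Trial design {8} describes "warning messages when predefined limits of frequent medication use are reached or passed", and the Discussion speaks of "additional warning messages if predefined thresholds of acute medication use are reached". On where the alert limits come from, Intervention description {11a} says only "Thresholds have been defined in accordance with the current ICHD-3 guidelines". It gives no number.

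**The concern.** A month on exactly 10 days of specific migraine medication, 15 days of simple analgesics or 15 headache days is an overuse or headache month under the definition. It is not one under the scoring sentence. The scoring sentence cannot be dismissed as a restatement of ICHD-3: it is marked as study-specific, and it shortens the required duration from more than three months to three months or more. A programmer could reasonably treat it as the operative rule.

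Three things depend on the choice: the event rate on which the sample size rests, agreement with the cited definition, and the in-trial notification of patients and investigators when the outcome occurs. The boundary also lies close to where the intervention acts, because alerts go out once a limit is reached. If the alert limit equals the endpoint limit, months ending exactly on the limit may be more frequent in the intervention arm.

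**Working it through.** **1. The two rules side by side**

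| Monthly count, specific migraine medication | Definition (10 or more) | Scoring sentence, literal (more than 10) |
|---|---|---|
| 9 | no | no |
| exactly 10 | overuse month | not an overuse month |
| 11 | overuse month | overuse month |

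The same one-day disagreement arises at 15 analgesic days and at 15 headache days.

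**2. Which patients change status**

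- 10, 10, 10 in three consecutive months: event under the definition, non-event under the literal sentence.
- 11, 10, 12: also changes, because the middle month breaks the run.
- 10, 10, then 7 and below: non-event under both, because no run of three is completed.
- 12, 12, 12: event under both.

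Every run that qualifies under the strict rule also qualifies under the inclusive one. For any given set of diaries the strict event rate is therefore equal or lower. This needs no assumption.

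**3. The plan's own sample size reproduces**

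Inputs from Sample size {14}: 10% against 4% (migraine), 40% against 25% (post-MO(H)), α = 0.05, power 0.80. Two-sidedness comes from Statistical methods {20a}. Pooled z-test, no continuity correction:

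n per arm = [1.960·√(2·p̄·(1−p̄)) + 0.8416·√(p₁(1−p₁) + p₂(1−p₂))]² / (p₁ − p₂)²

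- Migraine, p̄ = 0.07: (1.960·√0.1302 + 0.8416·√0.1284)² / 0.06² = (0.7072 + 0.3016)² / 0.0036 = 282.7, so 283.
- Post-MO(H), p̄ = 0.325: (1.960·√0.43875 + 0.8416·√0.4275)² / 0.15² = (1.2982 + 0.5503)² / 0.0225 = 151.9, so 152.

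Both match the protocol. No stated figure is in dispute.

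**4. Illustration of the shift in event rate**

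The document gives no distribution of monthly intake days, so everything here is assumed: the 10-day class only, twelve 28-day months, and an event defined as three consecutive qualifying months. The mean is set so that the inclusive rule gives the planned control rates. Model A has binomial monthly counts and a between-patient SD of 2 or 3 days. Model B has a logit-normal daily intake probability, between-patient SD 0.6 or 1.0, month-to-month SD 0.2, and a screening month below 10 days.

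| Control rate, inclusive | Strict, model A | Strict, model B |
|---|---|---|
| 10% | 4.6–5.7% | 5.5–6.2% |
| 40% | 25–29% | 28.6–29.6% |

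If the planned relative reductions (60%; 15/40 = 37.5%) also held under the strict rule, power at the planned size would be:

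- Migraine, 283 per arm: 46–55% (A) and 53–58% (B). For example, 5.5% against 2.2% gives 53%.
- Post-MO(H), 152 per arm: 53–60% (A) and 60–62% (B). For example, 28.6% against 17.9% gives 60%.

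**5. Illustration of a between-arm effect**

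Add to model A that the alert limit is also 10, and that a share of intervention patients stops on exactly day 10 in every month that would otherwise go higher, with no further change.

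- Share 0%: no between-arm difference under either rule.
- Share 60%, inclusive rule: intervention equals control (10% and 40%).
- Share 60%, strict rule: 1.9–2.3% against 4.6–5.7% (power 0.45–0.53), and 10–12% against 25–29% (power 0.93–0.97).

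In this scenario post-MO(H) power under the strict rule rises, whereas in step 4 it falls. The two steps rest on different assumptions about the effect and must not be combined.

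**The case against.** The strongest reply is that the boundary is already settled. The section opens by tying the outcome to ICHD-3, the scoring sentence refers back to thresholds just defined inclusively, the eligibility criteria use the same inclusive limits, and nowhere does the article print a strict limit for an endpoint threshold. On that view *exceeded* is loose wording. This largely stands: at-or-above is the better-supported reading, and a reader who concluded that the boundary is undefined would go too far. What remains is that the sentence a programmer would implement says something else.

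A reader might also infer that the boundary decides whether a patient who heeds the alert counts as an event. The documents do not support that in general. The endpoint needs three consecutive months, so someone who cuts intake below the limit after an alert is a non-event under both rules. The protocol also describes more than a same-month stop signal: a short-term appointment under the adherence measures {11c} and, in the Discussion, physician intervention. The scenario in step 5 ignores both. It further assumes that the alert and endpoint limits are equal, which the intervention description makes plausible but does not state.

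Nor do the alert passages contradict the definition. An alert sent when a limit is reached or passed is compatible with an inclusive endpoint.

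Finally, the suggestion that whoever codes the endpoint would choose the result is not supported. Outcomes are notified during the trial and app-based events are confirmed at visits, so a rule must already operate during conduct.

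**Conclusion.** The point holds as an internal contradiction in the wording of the primary endpoint. The definition is inclusive, the study-specific scoring sentence is literally strict, and the inclusive reading has the better support. Literal coding would depart from the cited definition, score months exactly at the limit as non-overuse, and give an equal or lower event rate. That much follows from the text alone.

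The size does not. The fall in control rates from 10% to roughly 5–6% and from 40% to roughly 25–30% is illustrative. It depends on assumed intake distributions, covers only the 10-day class, leaves out the 15-day analgesic and headache-day limbs, and takes the planned rates to belong to the inclusive rule. The power figures additionally hold the planned relative reductions fixed. A differential effect between arms is possible, but it rests on an unstated alert limit and on stopping exactly at that limit often enough to decide a three-month run. It should not be presented as an expected distortion of the result.

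**What to change.** In Outcome assessment, change the scoring sentence so that the endpoint is met when the intake or headache-day thresholds are *reached or exceeded*. The day-count operator then matches the ICHD-3 definition already cited. Use that single operator in the app-based event derivation, the notification of outcomes to patients and investigators, and the analysis code. A sensitivity analysis with the strict rule is optional and would show how many patients sit on the boundary in each arm.

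The cost is one phrase in the protocol and a check of one operator wherever the endpoint is derived. The downside is that the estimated effect may be somewhat smaller under the inclusive rule, because a month that ends on the limit after an alert still counts. No change to the alert limit is proposed.
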